**Gaps in knowledge**

There are wide differences in the prevalence of chronic diseases in developing and developed countries. These differences could be associated with the socio economic and cultural conditions in which people live, study and work. The interventions which are workable in developed countries may not be workable and effective in developing countries and there might be a need of different interventions in urban and rural areas. The most efficient interventions have occurred at community level for prevention and control of various chronic diseases, whenever the intervention was permanent or maintained for long periods, and relied on the continuous education of community health workers that had a constant interference inside the population covered. It is important that the intervention should be sustainable, otherwise health workers at some point may lose interest, and therefore, it may be worth experimenting to involve a family member who is young to bring change.[^78^](#_ENREF_78)

Literature on chronic diseases like hypertension and diabetes were mostly done on patients and not much is known about interventions among adolescents except for obesity. Less focus is on prevention of chronic diseases and more studies are on the treatment of the diseases. At present there are some indications that adolescents in the upper end of the cholesterol and blood pressure distribution seem to stay there later.[^79^](#_ENREF_79)^,^ [^80^](#_ENREF_80) Thus, not only should prevention be aimed at the whole population, it also may be useful to give special attention to adolescents to reduce the risk factor distribution.[^81^](#_ENREF_81)

Some studies have focused their actions in adolescents, especially on students, because they were more influenced by educational activities of prevention, and the knowledge ac­quired by them would spread more easily to their family and to society.[^49^](#_ENREF_49) But, none of the studies among the students and adolescents have looked into the effect of intervention on behaviors of teachers and parents of the adolescents.

From the previous intervention studies, it is evident that only those interventions are successful in which the researcher is involved in the intervention and it is the direct intervention. The indirect interventions are not that successful and also the intensity and duration of the intervention is very important for it to be a success.

Most of the interventions lack sustainability which reduces its ultimate impact.

**AIM**

To assess the effect of school-based health promotion intervention package among adolescents, their parents and teachers on the risk factors (unbalanced diet, physical inactivity, obesity, use of tobacco & alcohol) of chronic diseases.

**Objectives of the study are to:**

1. Measure behavioural (unbalanced diet, physical inactivity, and tobacco & alcohol use), anthropometric (height, weight, waist circumference, hip circumference, mid-upper arm circumference, subscapular and triceps skinfold thickness), physiological (blood pressure) and biochemical (fasting plasma glucose and urinary sodium excretion levels from 24-hour and spot urine samples) risk factors of chronic diseases among adolescents, their parents and teachers
2. Develop and implement a health promotion intervention package of six-month duration in school settings
3. Determine the effect of the intervention package on behavioural, anthropometric (height and weight), physiological (blood pressure), and biochemical (urinary sodium excretion levels from spot urine samples) risk factors of chronic diseases among adolescents

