**Population**

The study will be conducted among students, their parents and teachers. As the study focuses mainly on the students and reaches out to their parents & teachers, the study population will be the individuals in the age group of 11-16 yrs for students, their parents & teachers up to age of 65 years.

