**Methods for Objective 1**

Quantitative data will be used to identify behavioral risk factors.

A baseline survey will be carried out where, demographic details of each participant such as name, age, sex, education, occupation, number of family members, annual income, and knowledge and practices about the risk factors of chronic diseases will be collected from students, parents and teachers. Anthropometric measurements, such as, height and weight, BMI, waist circumference, hip circumference, waist-hip ratio, skin-folds (triceps and sub-scapular), mid- upper arm circumference and maximum hand grip strength will be taken before and after intervention. This will be one of the parameter to assess the effectiveness of the intervention. Hypertension will be checked for students, parents and teachers in pre & post intervention in both intervention and control arm.

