**Methods for Objective 3:**

Effectiveness of the intervention will be measured using following indicators in the baseline and end line sample survey among adolescents:

Before the intervention, perceptions, knowledge and practice of case and control group adolescents will be assessed for the chronic diseases and their risk factors with the help of a questionnaire. This will help in measuring the extent of behavior change. This questionnaire will be used as one parameter to assess the effectiveness of the intervention as the same questionnaire will be used after the completion of the intervention. This will help in assessing the improvement of the perception, knowledge and practices.

For objective measurements, anthropometric measurements, such as, height and weight, along with physiological measurement (blood pressure), biochemical measurement (24-hour excretory sodium through spot urine samples) will be taken before and after intervention. This will be the second parameter to assess the effectiveness of the intervention. The net changes in primary and secondary outcome measures among parents and teachers will be considered as exploratory analysis,

| **Intervention** | **Impact** | |
| --- | --- | --- |
|  | **Direct** | **Indirect** |
| Diet | Participant | Family |
| Physical activity | Participant | Family |
| Alcohol | Participant | Family |
| Smoking | Participant | Family |

**Table:** Impact of different interventions on the participants and their families.

| **Expected outcome of Intervention** |
| --- |
| 1. Increase in knowledge about various chronic diseases and their risk factors 2. Positive response for behavior for diet and physical activity 3. Increase in normal BMI and waist-hip ratio 4. Reduction in risk factors of chronic diseases, such as, decrease in salt and sugar intake and increase in iron intake. 5. Reduction in the consumption of junk food. 6. Adherences to the medicine among those having chronic diseases. 7. Change in stage of behavior |

**Table:** Expected outcomes of intervention package

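### The protocol's sections disagree on which anthropometric outcome shows the effect in adolescents, and none names an age- and sex-standardised measure that answers the obesity aim

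*Protocol*

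**What the plan says.** The Aim is to assess the package's effect "on the risk factors (unbalanced diet, physical inactivity, obesity, use of tobacco & alcohol) of chronic diseases". Obesity is thus one of the risk factors the trial sets out to change.

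Objective 3 undertakes to "Determine the effect of the intervention package on behavioural, anthropometric (height and weight), physiological (blood pressure") and spot-urine sodium. Its anthropometric part is height and weight only. The Methods for Objective 3 repeat the pair: "For objective measurements, anthropometric measurements, such as, height and weight, along with physiological measurement (blood pressure") and urinary sodium, taken before and after the intervention. On the role of these measurements they add: "This will be the second parameter to assess the effectiveness of the intervention".

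Two other places differ. The Methods for Objective 1 list "Anthropometric measurements, such as, height and weight, BMI, waist circumference, hip circumference, waist-hip ratio", followed by skinfolds, mid-upper arm circumference and grip strength, also taken before and after, and state: "This will be one of the parameter to assess the effectiveness of the intervention". The expected-outcomes table, which sits under Methods for Objective 3, includes "Increase in normal BMI and waist-hip ratio".

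Under Population, "the study population will be the individuals in the age group of 11-16 yrs for students"; the Sampling Framework gives 10 to 16 years for the same grade. No section names a growth reference, a BMI z-score, or a cut-off for overweight or obesity.

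**The concern.** An objective should say which result will count as an effect. Here a reader who starts from Objective 3 would look at height and weight, and a reader who starts from the Objective 1 methods or the expected outcomes would look at BMI and waist-hip ratio.

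The pair in Objective 3 is also a weak match for the aim. A diet and activity package is not meant to change height, and height is not a modifiable risk factor for chronic disease. Weight in a growing adolescent reflects growth as well as fatness. BMI combines the two, but whether a given BMI is normal at these ages depends on age and sex, so the expected rise in normal BMI cannot be evaluated until a reference is fixed.

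Two things are at stake. The trial could report on the anthropometric objective without answering the obesity question. And with several measures each described as showing effectiveness, the choice of which to stress could be made after the endline data are seen.

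**Working it through.** The protocol states no effect size, standard deviation or sample size for height, weight, BMI or obesity, so there is no planned figure to reproduce. The check is a comparison of sections, followed by an illustration on assumed values.

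**Step 1. Sections side by side.**

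| Section | Anthropometric content | Role given |
| --- | --- | --- |
| Aim | Obesity | Target risk factor |
| Objective 1 | Height, weight, waist, hip, mid-upper arm, two skinfolds | Measure risk factors |
| Objective 3 | Height, weight | Effect among adolescents |
| Methods for Objective 1 | The Objective 1 items plus BMI, waist-hip ratio, grip strength | Before/after measure of effectiveness |
| Methods for Objective 3, text | Height, weight (as examples) | Second parameter of effectiveness |
| Methods for Objective 3, expected outcomes | BMI, waist-hip ratio | Expected result |
| Hypotheses; sample-size table | None | None |

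Objective 3 drops the circumferences and skinfolds listed in Objective 1, so no direct measure of body fat or fat distribution remains in the effect objective. The Methods for Objective 1 name ten measures: height, weight, BMI, waist, hip, waist-hip ratio, triceps skinfold, subscapular skinfold, mid-upper arm circumference and grip strength. No section ranks them.

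**Step 2. Does weight alone track adiposity at these ages?** If BMI stays constant while height goes from h to h + g (in metres), weight changes by

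BMI × [(h + g)² − h²].

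Assumed inputs, none from the documents: h from 1.45 to 1.65 m, BMI from 16 to 22 kg/m², growth from 1 to 4 cm over the six months.

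- Lowest: 16 × (1.46² − 1.45²) = 16 × 0.0291 = 0.5 kg.
- Middle: 18 × (1.57² − 1.55²) = 18 × 0.0624 = 1.1 kg.
- Highest: 22 × (1.69² − 1.65²) = 22 × 0.1336 = 2.9 kg.

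So pupils could gain about 0.5 to 2.9 kg with no change in BMI. Conversely, the same weight can mean very different BMI. For 50 kg, BMI = 50/h²:

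| Height (m) | 1.40 | 1.50 | 1.60 | 1.70 |
| --- | --- | --- | --- | --- |
| BMI (kg/m²) | 25.5 | 22.2 | 19.5 | 17.3 |

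**Step 3. What the design removes.** Schools are randomised with a concurrent control arm, and the Study Design section compares net changes. Growth common to both arms drops out of that difference. Variation in growth between pupils remains as noise in weight and height.

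**Step 4. Are the inputs for a better measure available?** Age and sex are collected at the baseline survey, and height and weight are measured before and after. An age- and sex-standardised BMI can be computed at both times, with age at endline following from age at baseline and the measurement dates.

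**The case against.** The strongest reply is that the bracket in Objective 3 lists measurements, not endpoints. The bracket in Objective 1 also omits BMI and waist-hip ratio, although both appear in that objective's methods, so height and weight may simply be what is needed to compute BMI. The Methods for Objective 3 introduce the pair as examples. BMI is already a before/after effectiveness measure in the Objective 1 methods and an expected outcome under Objective 3. The growth reference and the model could stand in a statistical analysis plan not shown here.

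Much of this stands. A reader of Objective 3 alone might infer that adiposity is not assessed, or that the effect is to be judged on raw weight and height and nothing else. The documents do not support either inference, because BMI is named elsewhere with an effectiveness role.

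A reader might also infer that growth will bias the comparison, or that chance age differences between six schools per arm will produce a spurious weight effect. That does not follow either. The control arm removes average growth. A chance difference between arms in weight level largely cancels in a comparison of changes, leaving only differences in growth rate, and chance imbalance is random error, not bias. The protocol contains nothing from which to size it. The Statistical Analysis section also plans t-tests by sex and regression for confounders, although it does not name age.

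The reply does not remove the disagreement between sections. The Objective 1 methods and the measurement table list BMI as an item separate from height and weight, so the shorter list in Objective 3 is not plainly shorthand for BMI. Computing details can be left to an analysis plan, but which outcome an objective is judged on should be fixed, and stated consistently, in the protocol.

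**Conclusion.** The point holds as one of internal consistency and construct validity in a supporting outcome. The aim includes obesity; Objective 3 and the text of its methods name height and weight; the Objective 1 methods and the expected outcomes name BMI and waist-hip ratio; and no measure standardised for age and sex is named anywhere. The consequences are a weak link to the obesity aim, extra noise from growth, and an open choice among ten anthropometric measures.

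It is not a finding of systematic bias, and no size in kilograms or centimetres can be put on an error in the treatment effect. The 0.5 to 2.9 kg in the working rests wholly on assumed heights, BMI and growth; it shows only that weight and adiposity can part company over six months. The weight of the point is moderate: obesity appears in neither hypothesis and in no row of the sample-size table, so the main behavioural comparisons are untouched. It should still be corrected before endline data are examined.

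**What to change.** - In Objective 3 and the Methods for Objective 3, name BMI-for-age-and-sex z-score, computed with a stated growth reference, as the anthropometric effect outcome.
- Analyse the endline z-score with the baseline value as covariate and with allowance for clustering by school.
- Give the proportion overweight or obese by the same reference as a supporting result. This would also define what a normal BMI means in the expected-outcomes table.
- Report raw height and weight as descriptive only.
- Reconcile these sections with the Methods for Objective 1 and with the waist-hip ratio entry among the expected outcomes: state whether waist-hip ratio and the other measures are secondary, exploratory or baseline description.

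The cost is a few lines of wording and of analysis code. Age, sex, height and weight are already collected, so no new measurement or visit is needed.

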**HYPOTHESIS**

**Null hypothesis:**

School-based health promotion intervention will not lead to any change in the dietary intake of salt (g/day), sugar (g/day), fruits (g/day), vegetables (g/day), physical inactivity (%), tobacco and alcohol use (%) among adolescents.

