**Alternate hypothesis:**

School-based health promotion intervention will decrease the dietary intake of salt (g/day) and sugar (g/day), increase the intake of fruits (g/day) and vegetables (g/day), and decrease the physical inactivity (%) and tobacco and alcohol use (%) among adolescents.

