**Sample size**

A total of 12 clusters were calculated based on the formula as shown below. Six clusters in intervention arm and six in control arm. As most of the schools in general have strength of 30 students in each section, the size of cluster (m) was taken to be 30 each from a randomly selected section of class 8^th^. Sample size for each indicator (risk factors: Unbalanced diet, physical inactivity, tobacco use and alcohol use) was calculated separately by using data from previous studies.

For quantitative data the sample size will be the same, i.e., 6 clusters in intervention arm & 6 in control arm for students, their parents & teachers in total. For qualitative data the sample size will be max up to 8 participants for each of the focus group discussion.

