**Formula used:**

**c = 1 + f [ π_0_(1 - π_0_)/m + π_1_(1 - π_1_)/m + k^2^ (π_0_^2^ + π_1_^2^) ] / (π_0_ - π_1_)^2^**

Where,

- c is the number of clusters per treatment arm
- f = 7.84 for 5% type I error and 80% power
- π_1_ is the expected proportion in the intervention arm
- π_0_ is the expected proportion in the control arm
- m is the number of individuals in each cluster (assumed equal in all clusters)
- k is the coefficient of variation in the (true) rates or proportions between clusters in each treatment arm

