**Sample size based on the risk factors**

| **Risk Factor** | ***π_0_*** | ***π_1_*** | ***K*** | ***C*** |
| --- | --- | --- | --- | --- |
| Inadequate fruits and vegetable intake^82^ | 0.852 | 0.596 | 0.025 | 12.2 |
| Excess salt intake^83^ | 0.223 | 0.162 | 0.094 | 12.1 |
| Sugar intake (g/day)^84^ | 0.507 | 0.355 | 0.041 | 12.5 |
| Physical inactivity^85^ | 0.232 | 0.162 | 0.099 | 12.1 |
| Tobacco use^85^ | 0.049 | 0.034 | 0.163 | 11.4 |
| Alcohol use^86^ | 0.345 | 0.242 | 0.057 | 12.4 |
| Total clusters selected: Twelve | | | | |

Schools will be selected randomly for control and intervention groups (based on the consent) from the list of randomly selected schools.

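### Seven adolescent outcomes share one null and one alternative that are not complementary, with no designated primary outcome, no success rule and no diet outcome sized on its hypothesised scale

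*Protocol*

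**What the plan says.** The Null hypothesis section reads "School-based health promotion intervention will not lead to any change in the dietary intake of salt (g/day), sugar (g/day), fruits (g/day), vegetables (g/day") and continues with "physical inactivity (%), tobacco and alcohol use (%) among adolescents". That makes seven outcomes: salt, sugar, fruits, vegetables, inactivity, tobacco and alcohol.

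The Alternate hypothesis section is directional and joins its items with 'and': "School-based health promotion intervention will decrease the dietary intake of salt (g/day) and sugar (g/day), increase the intake of fruits (g/day") and so on through the same list.

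The Sample size section states that "Sample size for each indicator (risk factors: Unbalanced diet, physical inactivity, tobacco use and alcohol use) was calculated separately". The formula that follows uses "f = 7.84 for 5% type I error and 80% power" and defines its two rates as proportions. The table has six rows. Fruits and vegetables share one row ("0.852 | 0.596 | 0.025 | 12.2"), and the sugar row is labelled in g/day but contains proportions: "Sugar intake (g/day)^84^ | 0.507 | 0.355".

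Methods for Objective 3 says that the "net changes in primary and secondary outcome measures among parents and teachers will be considered as exploratory analysis". This is the only mention of primary outcome measures, and no section says which they are. Statistical Analysis lists t-tests, chi-square tests and multivariable regression, without a test level or an order of outcomes.

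**The concern.** The null and the alternative leave a large gap between them. If salt intake falls and tobacco use does not change, the null is contradicted but the alternative, read literally, is not met. The protocol does not say how such a result should be reported, and mixed results are the likeliest kind with seven outcomes.

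Because no outcome is named as primary, the headline result can be chosen after the data are seen. The choice is wider than the seven: the third objective adds height, weight, blood pressure and urinary sodium, and the table of expected outcomes adds knowledge, BMI, waist-hip ratio and others.

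The sample size does not settle the matter. It treats six prevalences as equal partners, each at the full 5%, and none of the four diet outcomes in g/day has a power calculation on its own scale.

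**Working it through.** **Sizing constant.** (1.96 + 0.84)² = 2.80² = 7.84. The stated f is reproduced and corresponds to a two-sided 5% test with 80% power. The same f is used for every indicator, with no split of alpha.

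**Hypothesis set against sizing.**

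| Hypothesised outcome | Sized as |
|---|---|
| Salt, g/day | proportion with excess intake, 0.223 vs 0.162 |
| Sugar, g/day | proportion, 0.507 vs 0.355 |
| Fruits, g/day; vegetables, g/day | one combined proportion with inadequate intake, 0.852 vs 0.596 |
| Inactivity, % | 0.232 vs 0.162 |
| Tobacco, % | 0.049 vs 0.034 |
| Alcohol, % | 0.345 vs 0.242 |

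The three percentage outcomes match a row. The four diet outcomes do not.

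**Reading 1: any one significant result counts.** Assume two-sided 5% tests, no true effects and independence.

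- Any significant result: seven outcomes, 1 − 0.95⁷ = 30.2%; six sized indicators, 1 − 0.95⁶ = 26.5%.
- Any significant result in the favourable direction: seven, 1 − 0.975⁷ = 16.2%; six, 1 − 0.975⁶ = 14.1%. The comparator for one test is 2.5%.

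The documents give no correlation between outcomes. Simulating equicorrelated normal test statistics (400,000 draws) gives this range for seven outcomes:

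| Pairwise correlation | Any significant | Any favourable |
|---|---|---|
| 0 | 30.2% | 16.2% |
| 0.3 | 27.2% | 13.7% |
| 0.5 | 23.0% | 11.5% |
| 0.7 | 17.8% | 8.9% |
| 0.9 | 11.3% | 5.7% |

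The favourable rate is 16.2/2.5 = 6.5 times that of a single test under independence, and 11.5/2.5 = 4.6 times at correlation 0.5.

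**Reading 2: all seven must succeed.** With no true effects, the simulated rate of all seven being significant is 0.03% at correlation 0.5 and 1.3% at 0.9, so false positives are rare. The difficulty is power. Rearranging the protocol's formula for c = 6 schools per arm and m = 30:

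- V = [π₀(1 − π₀) + π₁(1 − π₁)]/30 + k²(π₀² + π₁²)
- power = Φ(√[(6 − 1)(π₀ − π₁)²/V] − 1.96)

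For salt, V = 0.309027/30 + 0.008836 × 0.075973 = 0.01097. Then √(5 × 0.003721/0.01097) = 1.302, and Φ(1.302 − 1.96) = 25%.

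| Indicator (prevalence) | Power at 6 per arm |
|---|---|
| Inadequate fruit and vegetables | 99.9% |
| Sugar | 75% |
| Alcohol | 49% |
| Inactivity | 31% |
| Salt | 25% |
| Tobacco | 9% |

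Joint success cannot be more likely than its least likely component. Even if every assumed effect is real, the chance that all six sized indicators succeed is therefore at most about 9%, whatever the correlation.

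These powers come from the stated formula and inputs. The table's C column (11.4 to 12.5) does not follow from them, and twelve is used as a total although c is defined per arm. That is a separate point.

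**The case against.** The strongest reply is that multiplicity adjustment is commonly left to a statistical analysis plan, which is not shown here. That stands: the absence of a correction method is not the defect. It does not cover the hypothesis and the primary outcome, which belong in the protocol because the sample size rests on them, and this protocol states its hypotheses in a form that cannot be adjudicated.

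The protocol also limits multiplicity in one respect, by making the parent and teacher outcomes exploratory. That deserves credit, but it leaves the adolescent outcomes unordered.

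A reader might infer that the trial has a 30% chance of falsely claiming that the intervention works. The documents do not support that:

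- The 5% is given only for sizing. Its use for testing is an inference.
- Six indicators are sized, not seven.
- The protocol has no any-one-suffices rule. One significant result would contradict the null, but the alternative joins all items.
- The 30% counts results in the harmful direction and assumes independence. A false favourable claim is at most about 16%.

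A reader might also double the number of tests because Statistical Analysis mentions separate work by sex. That sentence concerns descriptive statistics and t-tests. The intervention effect is assigned to multivariable regression, with no split by sex, so fourteen confirmatory tests cannot be read into the plan.

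**Conclusion.** The concern holds as a defect of the stated hypotheses. They are not complementary, no success rule is given, primary outcomes are mentioned but never designated, and no diet outcome as hypothesised has a matching power calculation.

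The error inflation is conditional. It needs an any-one rule, two-sided 5% tests and no true effects, and the upper figures also need independence. Under the opposite reading false positives are rare, but the design could hardly succeed. Neither reading gives a workable confirmatory test, so the protocol has to choose. This should be corrected, and it can be done without redesigning the trial.

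**What to change.** Before unblinding or analysis:

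1. Designate one primary outcome among adolescents, chosen by the investigators on relevance, and state the scale on which it will be both analysed and sized. By the protocol's own formula, only the combined prevalence of inadequate fruit and vegetable intake reaches 80% power at 6 schools of 30 per arm. That is information for the choice, not a reason to make it, and the power does not carry over to fruits or vegetables in g/day. A g/day primary needs its own calculation.
2. Restate the null and the alternative as the intervention-minus-control difference in that outcome, tested at two-sided 5%.
3. Treat the other hypothesised outcomes as secondary with Holm adjustment. If combined fruit and vegetable intake is primary, five remain (salt, sugar, inactivity, tobacco, alcohol) and the first threshold is 0.05/5 = 0.010.
4. If no primary is wanted, apply Holm across all hypothesised outcomes. With seven, the first threshold is 0.05/7 = 0.0071.

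The cost is protocol wording and a stricter threshold for secondary outcomes. The option without a primary costs more. At 0.0071 the constant f rises from 7.84 to 12.47, and the protocol's formula then asks for 3.5 clusters per arm for fruit and vegetables but 10.0 for sugar and more for every other indicator, against the 6 planned.
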